### **Cost-Effectiveness Measures**

To establish the cost-effectiveness of the mentoring package, the following will be assessed:

- Referral on for secondary care opinion or intervention, or for diagnostic imaging.
- Use of prescription medication.
- Costs of physiotherapy intervention (number and type of attendances)
- Return to work
- Costs associated with the training of physiotherapists

The rationale and description of this element of the study is developed and explored in the economic evaluation section along with details of analysis.

The quantitative data collection for this study is summarized below in table 1.

**Table 1: Summary of Quantitative Data Collection**

| Dimension measured:                                                                                                 | Rationale for dimension:                                                                                                                                          | Measurement tools:                                                                              | Rationale for tool:                                                                                                                                                                                                                                                                                                                                                                                           |
|---------------------------------------------------------------------------------------------------------------------|-------------------------------------------------------------------------------------------------------------------------------------------------------------------|-------------------------------------------------------------------------------------------------|---------------------------------------------------------------------------------------------------------------------------------------------------------------------------------------------------------------------------------------------------------------------------------------------------------------------------------------------------------------------------------------------------------------|
| Patient outcome:
•Function
•Health-related quality of life
•Patient satisfaction
•Patient self-efficacy | The lack of research examining the link between therapist training and patient outcomes, despite multiple calls for such research to be undertaken as a priority. | Patient Specific Functional Scale (PSFS)                                                        | 1. The provision of numerical rating scores that will be comparable across body regions.
2. Focus on function in line with WHO ICF.
3. Responsiveness of patient-specific tools.                                                                                                                                                                                                                        |
|                                                                                                                     |                                                                                                                                                                   | EuroQuol (EQ-5D)                                                                                | 1. Broad application to a wide range of health conditions and treatments.
2. Provision of a simple descriptive profile and single index value for health status, allowing for comparison across clinical presentations, and cost utility analysis.                                                                                                                                                         |
|                                                                                                                     |                                                                                                                                                                   | MedRisk Instrument for Measuring Patient Satisfaction With Physical Therapy Care (MRPS)         | 1. Strong psychometric properties assessed on a large, diverse population.
2. Validation for use in an outpatient physiotherapy environment.
3. User-friendliness.
4. Satisfaction of criteria recommended by multiple authors for an appropriate patient satisfaction questionnaire (use of negative phrasing, multi-dimensional measurement and Likert scale, and self-completion by the patient). |
|                                                                                                                     |                                                                                                                                                                   | Patient Activation Measure (PAM)                                                                | 1. Multiphase psychometric testing to confirm its validity and reliability.
2. Maintains precision across different demographic and health status groups.
3. Identified for use at the aggregate level to evaluate and compare the efficacy of interventions.                                                                                                                                           |
| Patient distress and anxiety                                                                                        | To cross reference and enhance primary and secondary outcomes                                                                                                     | Örebro Musculoskeletal Pain Questionnaire (ÖMPQ)                                                | 1. Predictive ability to identify patients who will have a poor outcome across acute, sub-acute or chronic musculo-skeletal conditions.
2. Predictive ability to identify patients who will have a poor outcome across different body regions.                                                                                                                                                             |
| Patient demographic and healthcare utilisation data                                                                 | To enable adequate risk adjustment of primary and outcomes and cost effectiveness analysis                                                                        | Questionnaire                                                                                   | Items previously shown in other studies to be useful for risk adjustment and cost effectiveness are included.                                                                                                                                                                                                                                                                                                 |
| Therapist Performance                                                                                               | Previous educational research has measured performance; assessment will allow for triangulation of patient outcomes data with that of therapist performance.      | University course M level descriptors for assessing therapist performance on clinical placement | 1. Accepted and established form of assessing performance on M level courses where clinical placements are used.
2. Supporting research for the construct.                                                                                                                                                                                                                                                 |

## Sample size

The primary outcome measure, the PSFS, shows that for any individual patient, the minimal detectable change (90%CI) for an aggregate of 3 or more activities is 2 points; the minimum detectable change (90%CI) for a single activity is 3 points. In this study, we are looking for a mean difference of 1 point greater improvement in PSFS scores of patients whose physiotherapists who have received the intervention compared with the PSFS scores of patients whose physiotherapists have not yet received the training, as well as a greater proportion of patients achieving the level of minimal detectable difference. The following data values were used for the power calculation: mean changes on the PSFS from usual training to the new training of 1 point, and a Standard Deviation within each group of 2. The standard deviation was on the basis of PSFS data collected from an audit of 191 patients who had received treatment at the University Health

Board physiotherapy department, which is a slightly more conservative estimate than standard deviation values of PSFS outcomes from published studies (Hefford et al., 2009, Young et al., 2010, Costa et al., 2009).

A paper published on the design and analysis of stepped wedge designs (Hussey and Hughes, 2007) investigated the statistical characteristics of the stepped wedge design for CRCTs, and through the use of theoretical calculations and simulation the authors outline a procedure for computing power in stepped wedge trials. Using this procedure, a power calculation was carried out by [name], Senior Lecturer in Statistics, Swansea University in discussion with the rest of the research team. The power calculation is summarised below:

### **Power calculation: summary**

Following the notation of Hussey & Hughes (Hussey and Hughes, 2007), and defining

- I to be the number of physios (the maximum available would be 18; assuming recruitment of two-thirds of the maximum to be a realistic prospect, so we are primarily interested in  $I = 12$ )
- T to be the number of time points (4 time points are required to allow baseline measures and for 3 clusters to cross over from control to intervention, so we are primarily interested in  $T = 4$ )
- N to be the number of observations per physiotherapist per time point.

The model is

$$Y_{ijk} = \mu + \alpha_i + \beta_j + \theta X_{ij} + \varepsilon_{ijk}$$

where  $Y_{ijk}$  is the  $k^{th}$  observation at time  $j$  for physiotherapist  $i$ , and we assume that there is a random physiotherapist effect, so

$$\alpha_i \sim N(0, \tau^2)$$

and some random variation across observations, so

$$\varepsilon_{ijk} \sim N(0, \sigma_\varepsilon^2)$$

with independence everywhere. The  $X_{ij}$  are indicator variates, with value 0 before the intervention, and the value 1 thereafter. The range of indices are  $i = 1, \dots, I; j = 1, \dots, T$  and  $k = 1, \dots, N$ . We take  $\beta_T = 0$  in order to avoid identifiability problems, and wish to consider  $\vartheta$ , the difference in means in the control and intervention group. The variance of  $\hat{\vartheta}$  is given in equation (8) in Hussey & Hughes (Hussey and Hughes, 2007), and its calculation requires the specification of  $\sigma_\varepsilon^2$  and  $\tau^2$ , with  $N$  appearing through

$$\sigma^2 = \frac{\sigma_\varepsilon^2}{N}$$

Omitting some algebra, statistical power, based on the usual 95% confidence level, is defined by

$$1 + \Phi(-1.96 - \Delta) - \Phi(1.96 - \Delta)$$

where

$$\Delta = \frac{\theta_A}{\text{Var } \hat{\theta}}$$

and  $\Phi(\bullet)$  is the usual cumulative distribution function for the standard Normal distribution, and is implemented in EXCEL as =NORMSDISTO.

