## Methods - Participants

There are some key questions to be clear in answering in the design of CRCTs: what is the unit of randomization, how and to whom is the intervention delivered and how and on whom is the outcome measured (Hussey and Hughes, 2007)? In this study, the physiotherapy sites (departments) are the unit of randomisation, the intervention is delivered to participating physiotherapists in these clusters, and the outcome is measured on clusters of consenting patients who are treated by these physiotherapists.

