### Eligibility criteria for participant clusters

As expertise is generally accepted to be context dependent (Alderson, 2010, Benner et al., 1996, Edwards and Jones, 2007, Eraut, 2006b, Jensen et al., 2007b, Resnik, 2007), all qualified physiotherapy staff from the Cardiff and Vale University Health Board whose majority of time (i.e. greater than 50%) is practised inside the musculoskeletal outpatient context will be eligible to participate in this study. There are two main exclusion criteria, namely members of staff who have already undertaken postgraduate placements as part of Master's education and so would have received similar clinical reasoning facilitation, and rotational staff due to the fact that they will not be present in the department for long enough for both interventions and long term follow up. Currently, the maximum potential number of participating therapists would be 18. It is envisaged that 12 physiotherapists would realistically be recruited and organized into 3 clusters of physiotherapy staff (clustering by site).

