### Settings and locations where the data will be collected

Patient outcome data will be collected at the first and last appointment of physiotherapy treatment at the six sites of outpatient musculoskeletal physiotherapy service delivery for the Cardiff and Vale University Health Board: The Barry Hospital, Cardiff Royal Infirmary, University Hospital Llandough, St. David's Hospital, University Hospital of Wales and Whitchurch Hospital. The 6 sites are organized into pairs for training purposes, and so to further reduce the risk of any potential contamination across sites, these pairs will form the 3 clusters which will be the unit of randomization as illustrated in figure 3. Long-term patient outcome data (12 months post-discharge) will be collected by participating physiotherapists by telephone contact.

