#### Base case details

- Here, we take  $\theta = 1$  (that is, assume that the average effect of the intervention is 1), and (based on calculations on previous data) set  $\sigma_\varepsilon = 2$ . The remaining calculations are laid out in the attached spreadsheet, where, for illustration, if we take  $N = 9, \tau = 1$  then

$$Var(\hat{\theta}) = 0.12576 \dots,$$

and

$$\Delta = 2.819574$$

so that the power is

$$1 + \Phi(-1.96 - 2.8196) - \Phi(-1.96 - 2.8196) \simeq 1 - \Phi(0.8596) \simeq 0.805$$

- This implies that, in order to achieve a power of 0.8, we need a total of  $4 \times 12 \times 9 = 432$  observations.

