#### Randomisation

The stepped wedge design is a one-way crossover design in which different clusters cross over (switch treatments) at different time points (Mdege et al., 2011). In addition, the clusters cross over in one direction only—typically, from control to intervention. The first time point usually corresponds to a baseline measurement where none of the clusters receive the intervention of interest. At subsequent time points, clusters initiate the intervention of interest and the response to the intervention is measured. More than one cluster may start the intervention at a time point, but the time at which a cluster begins the intervention is randomized (Brown and Lilford, 2006, Hussey and Hughes, 2007).

Enrollment: participating physiotherapists will be recruited by the lead researcher by invitation on the basis of inclusion criteria. They will be approached by the lead researcher, and issued with participant information sheet version 2.0 (see appendix C). The lead researcher will also obtain written consent with participant consent form version 2.0 (see appendix C). During data collection periods, patients will be recruited by their physiotherapist, and issued with patient information sheet version 1.0 (see appendix B). The physiotherapist will also obtain written consent with patient consent form version 1.0 (see appendix B).

Sequence generation: once consented by the lead researcher, participating therapists will be directed to the clinical mentors. The clinical mentors will then randomly allocate the clusters of physiotherapists (clustering by site) to the sequence of intervention (to receive the intervention in time period 2, 3 or 4), by computer programme (Randomization.com, 2008).

Allocation concealment: The sequence generation will be performed by the allocated mentor, in order to ensure that this sequence allocation will be adequately concealed from the lead researcher, who will remain blinded to the sequence until after the data collection and analysis period is completed. These measures for blinding, sequence generation and allocation concealment are implemented to reduce the risk of bias, as highlighted by the Cochrane risk of bias tool (Armijo-Olivo et al., 2010, Lundh and Gotzsche, 2008).

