### **Statistical methods**

The analysis of stepped wedge trials has been clearly outlined in a published paper (Hussey and Hughes, 2007) and recommends processes for analysis of cluster-level means and individual level analysis in scenarios where cluster sizes are equal or unequal, and where variance is known or unknown. Processes for between cluster and within cluster analyses are outlined in order to avoid confounding the treatment effect with changes over time; these processes will form the basis for the statistical analysis for the study. If no temporal effects are found influencing the outcome, then a within-cluster analysis can be used to estimate the treatment effect. Statistical analysis will involve a classical ANOVA (so observations belong to one of two groups, each assumed to be independent of the others), supplemented by a random intercept which will reflect systematic differences across different clusters. Similar statistical methods have been used in other published stepped wedge trials (Schnelle et al., 1992, Bailey and Archer, 2004, Mdege et al., 2011).

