
External threats to validity in this study could occur from the narrow characteristics of participants in the experiment, care must be taken not to generalize to individuals who do not have the characteristics of participants. Therefore, while methods and results may be of interest to - and have relevance for - other allied health professions, additional experiments would need to be performed to ascertain whether similar results are elicited. Likewise, due to the narrow characteristics of the setting of participants in this

experiment (musculo-skeletal outpatients), care must be taken not to generalize to individuals in other settings (inpatient settings) without further experimentation.

Other threats to validity could involve statistical conclusion threats which occur from inadequate statistical power or violation of statistical assumptions leading the researcher to draw inaccurate inferences or conclusions from the data. In addition, construct validity can be threatened when the researcher uses inadequate definitions and measures of variables. The measures of variables have already been outlined as appropriate, for the variables that have been accurately defined, and the research study has been appropriately powered.

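### The stated power of 0.805 is for 12 independent physiotherapists; a 5-df test at the level of the 3 randomised site pairs has about 0.60, and less if site pairs drift separately

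*Protocol*

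**What the plan says.** **Randomisation.** Methods - Participants states that "the physiotherapy sites (departments) are the unit of randomisation". Settings and locations says that the six sites are paired and that "these pairs will form the 3 clusters which will be the unit of randomization as illustrated in figure 3". Eligibility criteria for participant clusters expects 12 physiotherapists "organized into 3 clusters of physiotherapy staff (clustering by site"). The Randomisation section has the mentors "randomly allocate the clusters of physiotherapists (clustering by site) to the sequence of intervention", with a start in period 2, 3 or 4.

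**Power.** Power calculation: summary defines "I to be the number of physios (the maximum available would be 18" and works with 12. Each physiotherapist has a random effect, all terms are independent, and there is no site-pair or site-pair-by-period term. The critical value is 1.96. Base case details reports 0.805 and continues "This implies that, in order to achieve a power of 0.8, we need a total of" 432 observations. The quantitative validity section, which appears twice in similar form, concludes that "the research study has been appropriately powered".

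**Analysis.** Statistical methods plans an ANOVA "supplemented by a random intercept which will reflect systematic differences across different clusters". It does not say whether these clusters are site pairs or physiotherapists.

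**The concern.** All physiotherapists in a site pair cross over together. A change confined to one pair during a 12-month step, such as staffing, case mix or local reorganisation, therefore moves the results of about four physiotherapists at once. The power model sets this shared movement to zero and uses a reference distribution suited to many independent units. If 0.805 is read as the power of the randomised design, a null result could be taken as coming from a trial with 80% power. If the analysis then followed the power model and pairs did drift separately, part of that drift would be credited to the mentoring programme with too small a standard error.

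**Working it through.** **Inputs.** From Sample size, Power calculation: summary, Base case details and Appendix E: effect 1, σ_e = 2, τ² = 1, T = 4, N = 9 per physiotherapist and period, I = 12. Four physiotherapists per pair are assumed; Appendix E's U = 24, W = 224 and V = 56 match this. Site-pair-by-period variance is not in the protocol, so a range is assumed.

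**1. The protocol's figure.** With s² = σ_e²/N,

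Var = I·s²·(s² + Tτ²) / [(IU − W)s² + (U² + ITU − TW − IV)τ²].

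- s² = 4/9.
- Numerator: 12 × 0.4444 × 4.4444 = 23.704.
- Denominator: 64 × 0.4444 + 160 × 1 = 188.444.
- Var = 0.12579, effect/SD = 2.820, power = 0.805. This agrees with Appendix E.

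**2. Change only the unit.** I = 3, N = 4 × 9 = 36, s² = 4/36 = 0.1111, U = 6, W = 14, V = 14.

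- Numerator: 3 × 0.1111 × 4.1111 = 1.3704.
- Denominator: 4 × 0.1111 + 10 × 1 = 10.4444.
- Var = 0.1312; power with 1.96 = 0.788.

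The unit swap costs 0.805 − 0.788 = 0.017.

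**3. Allow for three randomised units.** Analyse the 12 pair-by-period means with pair, period and intervention effects.

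- Residual df = 12 − 3 − 3 − 1 = 5.
- The intervention indicator has a sum of squares of 0.8333 after removing pair and period effects.
- Var = 0.1111/0.8333 = 0.1333.
- Power from the noncentral t distribution on 5 df = 0.596 (0.594 in 40,000 simulated trials).

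**4. Add assumed site-pair-by-period variance.** In the pair-means test, Var becomes (0.1111 + variance)/0.8333. The weighted column is generalised least squares under the correct model with known variance components, referred to t on 5 df. The type I column is the normal test from the therapist-intercept model when the extra variance exists but is ignored: 2Φ(−1.96 × √(0.12579 / true Var)).

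| Assumed variance (SD, PSFS points) | Power, pair means, 5 df | Power, weighted model, 5 df | True Var of therapist-level estimate | Type I error of therapist-level z-test |
|---|---|---|---|---|
| 0 | 0.60 | 0.62 | 0.1258 | 0.050 |
| 0.02 (0.14) | 0.53 | 0.56 | 0.1473 | 0.070 |
| 0.04 (0.20) | 0.48 | 0.50 | 0.1688 | 0.091 |
| 0.10 (0.32) | 0.36 | 0.39 | 0.2332 | 0.150 |
| 0.20 (0.45) | 0.27 | 0.30 | 0.3407 | 0.234 |

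For scale, 0.02 is 0.5% of the residual variance of 4 (0.02/4), and 0.20 is 5%.

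**The case against.** **The count of 12 against 3 is not the cause.** A reader might infer that the loss comes from powering on 12 units in place of 3. Step 2 does not support this: the protocol's own formula gives 0.788 with 3 pairs. The loss comes from the normal reference with so few randomised units and from the omitted pair-level variation. This objection stands.

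**The 0.60 belongs to one choice of test.** With zero site-pair-by-period variance, a therapist-level t test on 32 df has power of about 0.76 (fixed therapist effects, Var 0.1333) or 0.78 (Var 0.1258). That is correct, but those degrees of freedom are available only if the independence assumption is true. The figure of 0.60 is power for a test that does not rely on it, and should be quoted that way.

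**The planned analysis is not shown to be anti-conservative.** A reader might infer that it is. Under the protocol's model the type I error is 5%, and the inflation depends on variances that the protocol does not give. Nor does Statistical methods place the random intercept at therapist level; elsewhere the word cluster means a site group. Small-sample corrections may sit in a SAP that is not at hand, so their absence is not itself a fault.

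**Period effects and a single health board help.** They absorb board-wide drift. They do not absorb drift in one site pair, and the protocol's reasons for clustering (staff at a site discuss the intervention; paired sites train together) make fully independent physiotherapists hard to assume.

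**Two further points carry no weight.** Three pairs allow only 3! = 6 orders, so a randomisation p-value could not fall below 1/6, but no such test is planned. The notation slips (effect divided by variance, a repeated term in the power line, τ² values labelled tau) leave 0.805 unchanged.

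**Conclusion.** The concern holds in a limited form. The value 0.805 is correct arithmetic for a model whose unit does not match the randomised unit. It is not the power of an analysis that respects three randomised site pairs. On the protocol's own effect, SD and patient numbers, such a test on 5 df has power of about 0.60 with no site-pair-by-period variance. It has about 0.5, 0.4 and 0.3 at assumed variances of 0.04, 0.10 and 0.20. The sensitivity discussion under Other cases covers the effect size, σ_e and τ, but neither the number of randomised clusters nor pair-level variation, so the unqualified statement of adequate power is not supported. The type I error figures of 9%, 15% and 23% are conditional on those assumed variances and on an analysis with a therapist intercept only.

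**What to change.** - In Sample size, Power calculation: summary, Base case details, Other cases and Appendix E, restate power at site-pair level with small-sample degrees of freedom. Add a sensitivity table over assumed site-pair-by-period variance, with the assumption labelled.
- Remove or qualify the claim of adequate power in both copies of the quantitative validity section.
- In Statistical methods, state that the primary analysis accounts for site pair, as the randomised unit, as well as physiotherapist, with fixed period effects and small-sample inference. Either a site-pair-by-period term or an analysis of pair-by-period means would do. If a SAP already specifies this, refer to it.
- Correct the three notation slips in the same edit.

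The cost is protocol wording and analysis code, a less favourable stated power and wider intervals. No extra patients are needed. The edit does not restore 80% power; it makes the stated precision match the design.

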Another challenge is the possibility that the full effect of the intervention may not be realized until several time intervals following implementation, for example, the intervention being 50% effective after the first time interval, 75% effective after the second time interval and 100% effective after the third time interval (Hussey and Hughes, 2007). Delayed effects from the intensive mentoring for clinical reasoning facilitation are possible, with physiotherapists requiring time to consolidate and make practice changes. The overall effect of these delayed effects would be to reduce power. Such delays can be modelled into the power calculations, and power can be recovered in part by adding additional measurement periods to the end of the trial. However, it is preferable to address this issue by making the time intervals sufficiently long to see the effects of the intervention realized in a single interval (Hughes, 2007, Hussey and Hughes, 2007). To address this, the clinicians who will act as clinical mentors in this study were asked to reflect on their own experience following mentoring programmes from their Masters courses, and estimate what time period they thought would be sufficient to consolidate knowledge and change practice. All responses estimated between 6-12 months. To this end, each time period will be 12 months long, with the intervention delivered at the beginning of the time period and the data collection at the end of the period to allow for the full effects of the intervention to make an impact.

One group of authors (Brown et al., 2008) highlight the amount of data collection required as the main disadvantage of the stepped wedge design, which could make the cost of using the design prohibitive, unless

the study can use routine, or other easily collected data. This study aims to collect patient outcome data at first and final appointments which is part of routine practice in the physiotherapy service at the Cardiff and Vale University Health Board. An additional collection of these outcomes will take place 12 months post discharge by telephone. Demographic and cost-effectiveness data will be collected at the same time in a single compiled questionnaire. This would certainly fit the description of routine, easily collected data.

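### The power model and a patient-level random-intercept analysis assume no therapist-by-step variation; 0.805 is the no-drift power, and no sensitivity case varies this

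*Protocol*

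**What the plan says.** - **Protocol, Power calculation: summary.** The model has fixed step effects, a treatment effect, patient-level error and one random term: "we assume that there is a random physiotherapist effect". It is completed "with independence everywhere". Two patients of the same therapist are therefore equally correlated whether they are seen in the same step or years apart.
- **Protocol, Base case details.** The power of 0.805 comes from N = 9 and tau = 1, introduced with "for illustration, if we take".
- **Protocol, Other cases, and Appendix E.** The text warns that power is sensitive to theta, sigma_e and tau. The spreadsheet varies tau and N. No therapist-by-step variance is given, justified or varied.
- **Protocol, Statistical methods.** The analysis is an ANOVA "supplemented by a random intercept which will reflect systematic differences across different clusters". The same section adopts a published stepped-wedge method as its basis and notes that this covers both cluster-level means and individual-level data. It does not say which level will be used.
- **Protocol, Challenges in using this design and how they will be addressed.** Time effects will be added to the model, and "each time period will be 12 months long".

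**The concern.** A constant therapist mean is a strong assumption in this trial, and the Protocol's own description points the other way. Each step brings a fresh group of patients for each therapist (Procedures). Control steps include continuing training with monthly mentoring (Control). The intervention is tailored to each therapist's reasoning errors (Scientific background and rationale), and learning style is acknowledged as a possible strong influence on how much each therapist gains (Validity approaches in quantitative methods). Uneven development before crossover and uneven response after it are both therapist-by-step variation.

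If that variation is present and the model has no term for it, patients in the same therapist-step are more alike than the model allows. A patient-level analysis then judges the training contrast against patient noise alone. At stake are the width of the confidence interval, the error rate of the primary test, and the statement that the study is appropriately powered. The issue would remain even if the 12 therapists were randomised individually.

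**Working it through.** **Inputs from the Protocol.** I = 12 therapists ("assuming recruitment of two-thirds of the maximum to be a realistic prospect"), taken as 4 per sequence. T = 4 ("4 time points are required to allow baseline measures and for 3 clusters to cross over from control to intervention"). N = 9, sigma_e² = 4, tau² = 1, theta = 1 ("assume that the average effect of the intervention is 1"), two-sided alpha 0.05. Appendix E gives U = 24, W = 224, V = 56.

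**Input not in the Protocol.** The therapist-by-step variance, written gamma². It is assumed below and shown as a range.

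**1. Reproduce the stated figure.** With s² = sigma_e²/N = 4/9 = 0.4444:

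Var = I·s²·(s² + T·tau²) / [(I·U − W)·s² + (U² + I·T·U − T·W − I·V)·tau²]

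- I·U − W = 288 − 224 = 64
- U² + I·T·U − T·W − I·V = 576 + 1152 − 896 − 672 = 160
- Var = 5.3333 × 4.4444 / (28.4444 + 160) = 0.1258; SE = 0.3547; Delta = 1/0.3547 = 2.8196
- Power = 0.805, as stated

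(The summary prints Delta as theta over the variance. The spreadsheet uses theta over the SD, as here.)

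**2. Allow drift, keeping total therapist variance at 1.** Let r be the correlation of a therapist's true mean between steps. Then tau² = r, gamma² = 1 − r, and s² becomes 4/9 + (1 − r).

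| r | s² | Var | SE | Power |
|---|---|---|---|---|
| 1 | 0.4444 | 0.1258 | 0.355 | 0.805 |
| 0.9 | 0.5444 | 6.5333 × 4.1444 / (34.8444 + 144) = 0.1514 | 0.389 | 0.729 |
| 0.8 | 0.6444 | 7.7333 × 3.8444 / (41.2444 + 128) = 0.1757 | 0.419 | 0.665 |
| 0.6 | 0.8444 | 10.1333 × 3.2444 / (54.0444 + 96) = 0.2191 | 0.468 | 0.570 |

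Reaching 0.8 would need 12 patients per therapist per step at r = 0.9 (48 × 12 = 576 in total) and 16 at r = 0.8 (768), against the planned 9 (432). If gamma² is instead added on top of tau² = 1, power is 0.789 at gamma² = 0.02, 0.726 at 0.10 and 0.658 at 0.20. These figures use the Protocol's normal reference; a t reference lowers them slightly.

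**3. Error rate if the drift is ignored at patient level.** Holding the model's components at base-case values and adding gamma² = 0.10, the true SE is 0.390 against a model SE of 0.355. The nominal 5% test then has error 2·[1 − Φ(1.96 × 0.355/0.390)], about 7.5%. At gamma² = 0.20 (true SE 0.422) it is about 10%. Simulated null trials of the random-intercept model with estimated components (4,000 per setting, total therapist variance 1) gave 5.1% at r = 1. Repeat runs gave 7.7–8% at r = 0.9, 9.8–10.5% at 0.8 and 13.8–14.4% at 0.6.

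**4. Error rate with a cell-level residual.** The 12 × 4 = 48 therapist-step means, with therapist and step effects, leave 48 − 12 − 3 − 1 = 32 residual degrees of freedom. That residual already contains gamma². Across 20,000 null trials per setting, type I error was 5.1%, 4.8%, 5.0% and 5.3% at r = 1, 0.9, 0.8 and 0.6.

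**The case against.** A reader might infer that the standard errors are too small as a matter of fact, that the false-positive rate exceeds 5%, and that 0.805 is an upper bound on power. The Protocol does not support any of these as stated.

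- **No drift figure is given.** Only the direction of the effect is certain; the correlations above are chosen for illustration. This stands.
- **0.805 is a maximum only with theta, sigma_e, tau and N fixed at the base case.** At N = 9 the same formula gives 0.851 at tau² = 0.22 and 0.934 at tau = 0. If the audit SD of 2 is a total SD, power at ICC 0.2 is 0.883 without drift and 0.819 at r = 0.9. With sigma_e = 2 and ICC 0.05, even r = 0.5 leaves 0.813. Risk adjustment could also lower the residual variance: an assumed 3.2 with r = 0.9 gives 0.798. This stands.
- **The inflation is not inevitable.** Statistical methods mentions analysis of cluster-level means, and step 4 shows that therapist-step means with an estimated residual hold about 5%. This stands, but the section does not choose that route, and the random intercept it describes applied to patient data would not be protected.
- **Detail of this kind is often left to an analysis plan, and the power method follows a published procedure.** That explains the omission. It does not supply the missing sensitivity case: the power section fixes the term at zero and then declares which inputs matter without naming it.
- **A therapist-by-step term does not reach the randomised unit.** The three site-pairs are randomised (Settings and locations where the data will be collected), and drift shared within a pair remains. This stands and limits the fix.

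**Conclusion.** The concern holds in conditional form. The power model, and the random-intercept analysis if run on patient-level data, set therapist-by-step variation to zero, and nothing in the Protocol tests that. The base case has little room for it: gamma² = 0.02 is enough to bring power under 0.80. At the base-case therapist variance of 1, moderate drift costs between about 8 and 24 points of power (0.805 to 0.729 at r = 0.9; to 0.570 at r = 0.6) and takes the patient-level test's error from 5% to between about 8% and 14%.

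These sizes rest on three assumptions: the chosen correlations, sigma_e = 2 read as the within-therapist SD, and tau = 1. With a smaller therapist variance the loss is much smaller. The arithmetic in the Protocol is not in error; 0.805 is right for the case it describes.

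**What to change.** - **Statistical methods.** Either add a random therapist-by-step effect to the patient-level mixed model, or specify an analysis of therapist-step means with an estimated residual. In both cases use the residual degrees of freedom of the cell-level model (about 32, not the 48 cells).
- **Base case details and Other cases.** Label 0.805 as the no-drift case at theta = 1, sigma_e = 2, tau = 1 and N = 9, and give power as a range over an explicit between-step correlation.
- **State the limit.** Neither option deals with drift shared within the three randomised site-pairs. As an assumed illustration, a site-pair-by-step variance of 0.02 alone takes base-case power to 0.741, and 0.05 takes it to 0.658.

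The cost is one model term or a choice of analysis level, plus restated power. Intervals will be somewhat wider and the power figure less favourable. If there is no drift, little is lost: the cell-level test still holds about 5%.
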